# GLOSSARY of Terms and Abbreviations

ASR Annual Safety Report

BMI Body Mass Index

CA Competent Authority

CI Chief Investigator

CRF Case Report Form

CRO Contract Research Organisation

GAfREC Governance Arrangements for NHS Research Ethics Committees

GCP Good Clinical Practice

HRA Health Research Authority

ICF Informed Consent Form

IPAQ International Physical Activity Questionnaire
JRMO Joint Research Management Office

NHS REC National Health Service Research Ethics Committee

NHS R&D National Health Service Research & Development

Participant An individual who takes part in a clinical trial

PI Principal Investigator

PIS Participant Information Sheet

QA Quality Assurance

QC Quality Control

REC Research Ethics Committee

SOP Standard Operating Procedure

TMG Trial Management Group

TRE Time Restricted Eating

# SUMMARY/SYNOPSIS

| **Short Title** | TRE |
| --- | --- |
| **Methodology** | Cohort Follow-up |
| **Research Sites** | 1. Queen Mary University of London  Health and Lifestyle Research Unit  [name]  London  [name] |
| **Objectives**  **/Aims** | Time-restricted eating (TRE) allows food intake during a period of eight hours each day. TRE showed promising results in animal studies and become popular with dieters. This is a pilot study to assess its acceptability and short-term effects by examining 1. Client adherence compared with other methods used with similar clients; 2. Weight loss compared with other methods used with similar clients; 3. Changes in heart risk factors; 4. Whether it would be worth conducting a bigger, controlled trial. |
| **Number of Participants/Patients** | 50 |
| **Main Inclusion Criteria** | - aged over 18 years, - BMI over 30kg/m2, or over 28kg/m2 with comorbidities - Speaks, reads, and understands English |
| **Statistical Methodology and Analysis (if applicable)** | Descriptive statistics will be used to report on the proportion of participants adhering to TRE; the 8-hour time frames most commonly selected; and client feedback ratings. Paired samples t-test will be used to examine any significant changes from baseline to follow-up in weight, BMI, blood pressure, and blood lipid profiles. Adherence rates to TRE and weight/BMI changes will be compared against previous weight-loss intervention cohorts (e.g. our previous trials, community weight clinic), via Chi-square analysis for categorical variables and ANOVA for continuous variables. |
| **Proposed Start Date** | Grant: November 2017  Recruitment: February 2018 |
| **Proposed End Date** | Recruitment: May 2018  Grant: November 2018 |
| **Study Duration** | 18 months (3m for set-up; 3m for recruitment; 6m for final follow-ups; 3m for write-up and study close) |

# INTRODUCTION

**Background**

Over a quarter of adults in England are obese, with obesity more prevalent in disadvantaged socioeconomic groups (1). Ill health resulting from obesity is considered to be responsible for about 10% of morbidity and mortality in the UK (2). The health burden from obesity is largely driven by an increased risk of type 2 diabetes, cancer and cardiovascular diseases (3).

Simple and effective weight loss interventions that are easy to disseminate are lacking. Intermittent fasting (IF) that involves intermittent periods of total or partial energy restriction alternated with non-restricted energy intake is one potentially promising approach.

There is preclinical evidence showing that in animals, regular periods of IF accompanied by no other food restrictions, generates weight loss and improvements in cardio-metabolic health (4–7). In these studies, IF generated a reduction in total cholesterol and triglycerides, an increase in high density lipoprotein (HDL) cholesterol and in some animal models, it reproduced some of the cardiovascular benefits seen with physical activity, such as improvements in blood pressure and heart rate and increased resistance to ischaemic injury. In humans, IF can generate weight loss and a range of associated benefits, with improvements in glucose metabolism and lipid profiles, particularly promising in terms of cardiovascular health (8–13).

In terms of clinical practice however, the approach has a notable limitation; the existing human studies typically used a rather harsh form of IF with fasting on two consecutive days and caloric restrictions during the rest of the week (14). Within tightly controlled trials, a proportion of clients are able to persist with this approach for the trial duration, but the approach is too difficult for most people and it is not used in clinical practice.

IF, however, can be also implemented in less severe formats, one of which is ‘Time-Restricted Eating’ (TRE) or ’16:8’ diet. TRE requires clients to consume food only within a specific ‘window’ period each day, typically over eight hours, and refrain from any eating outside of this window. The simplicity of the approach could be useful particularly to disadvantaged client groups that rarely engage with more intensive and demanding interventions (15).

In terms of evidence available so far and any pilot data, animal studies suggest that even in this much simplified format, TRE still conveys benefits (16). Some human data are now also available, coming from a somewhat non-traditional application. Due to its supposed effects on muscle mass and fat, TRE has become popular among athletes and body builders. Two recent small RCTs found some benefits in resistance-training men (17, 18). A recent conference presentation reported that TRE practiced by 11 participants over 4 days reduced swings in hunger and increased fat and protein oxidization (19).

This is a proposal to evaluate the acceptability and short-term effects of TRE in an inexpensive and quick pilot study focusing on clients from areas of high social deprivation who are most likely to benefit from this particular approach, compared to other diets that require calorie counting and much more extensive behaviour change.

# TRIAL OBJECTIVES

**Primary Objective**

The primary objective of the study is to determine the feasibility of the TRE approach by examining adherence to TRE and retention rates.

**Secondary Objectives**

Secondary objectives include TRE effects on changes in weight, blood

pressure and lipid profile, client feedback, and, provided the intervention is

feasible and the efficacy results are encouraging, effect estimates to inform

any future randomized trial of the intervention.

**Primary Outcome**

The primary outcome is the adherence to TRE over a period of 3 months, specifically the average number of days on which TRE was adhered to. We will also monitor the retention rates at 6 weeks, three months and 6 months, defined as the proportion of participants who adhere to TRE at least once a week; and the drop-out rate defined as the proportion of participants who do not attend the 3 month follow-up session. We will compare retention and drop-out rates with those in our previous trials and community clinics.

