**TRE intervention**

Participants will be asked to consume all their food during an 8 hour period each day for the next three months. Over the remaining 16 hours each day, participants can drink, but only non-calorie drinks (e.g. water or coffee/tea with no milk or sugar). Participants will be free to choose which 8-hour period they would like to eat in.

**Follow-up visits and calls:** Participants will attend at one and six weeks, to provide measures of weight and to discuss their progress. They will also receive phone calls at weeks 2, 3, 4 and 5, that will monitor progress and collect data on adherence.

**12 week follow-up visit**: Participants will attend at 12 weeks to provide measures of weight and blood pressure, and a blood sample for lipid profile and to report on their adherence to TRE and provide TRE ratings.

**Final follow up visit:** Participants will attend at 6 months to provide measures of weight and blood pressure, and to report on their adherence to TRE and provide the final TRE ratings.

Participants will receive £10 at the 6, 12 week and 6 month visits as a compensation for their time and travel. Participants providing a blood sample at baseline and 12 weeks, will also receive £10 for each sample given.

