***Final follow up at 6 months:***

- Weight
- Blood Pressure
- Number of weeks on which TRE was adhered to
- 8-hour time periods selected.
- Ratings of TRE helpfulness, TRE difficulty, ratings of hunger on days TRE was adhered to

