**Statistical Analysis**

Descriptive statistics will be used to report on proportions of participants adhering to TRE; the 8-hour time frames most commonly selected; and client feedback ratings. Paired samples t-test will be used to examine any significant changes from baseline to follow-up in weight, BMI, blood pressure, and blood lipid profiles.

Adherence rates to TRE and weight/BMI changes will be compared against previous weight-loss intervention cohorts (e.g. our previous trials, community weight clinic), via Chi-square analysis for categorical variables and ANOVA for continuous variables.

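### Retention is defined as TRE use at least once a week, which is not retention in the study and has no stated counterpart in the cohorts it is compared with

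*Protocol*

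**What the plan says.** The Protocol's Primary Objective is feasibility, judged by adherence to TRE and by retention. The Primary Outcome section then sets three quantities:

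- adherence over 3 months, "specifically the average number of days on which TRE was adhered to";
- retention at 6 weeks, three months and 6 months, "defined as the proportion of participants who adhere to TRE at least once a week";
- "the drop-out rate defined as the proportion of participants who do not attend the 3 month follow-up session".

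It continues: "We will compare retention and drop-out rates with those in our previous trials and community clinics". The first aim in the Synopsis is "Client adherence compared with other methods used with similar clients", and the Statistical Analysis section states that "Adherence rates to TRE and weight/BMI changes will be compared against previous weight-loss intervention cohorts". Secondary Outcomes likewise refers to other weight-loss cohorts.

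The regimen is daily. Under TRE intervention: "Participants will be asked to consume all their food during an 8 hour period each day for the next three months". Under Subject withdrawal, people who stop TRE are still followed at 6 weeks and 3 months unless they decline. The adherence item listed for the 6-month visit is "Number of weeks on which TRE was adhered to".

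**The concern.** Retention usually means remaining under observation. Here the word names a second and weaker adherence measure, so two of the three feasibility quantities describe use of TRE. Only the drop-out rate describes staying in the study, and it exists at 3 months alone. A pilot meant to show whether a larger controlled trial is worthwhile also needs to know how many people return at each visit.

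The comparison adds a second problem. A rate defined by use of TRE cannot be carried over as it stands to a cohort that followed another method. The Protocol does not say what will stand in for it. If attendance or some other measure of continued treatment is used, two different quantities will be compared under one name, in a comparison that serves the study's first stated aim.

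**Working it through.** The Protocol states no retention figure to reproduce. The sample size is 50, described as pragmatic. The inputs are the once-a-week threshold (Primary Outcome), the daily regimen (TRE intervention), continued follow-up of people who stop TRE (Subject withdrawal) and n = 50 (Sample Size).

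**1. Threshold against regimen.** One day in seven is 1/7 = 14.3% of prescribed days. Over 12 weeks that is 12 of 84 days, so a participant can miss 72 of 84 (86%) and still meet the threshold.

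**2. Retention and drop-out are not complements.** Of 50 enrolled, let A attend at 3 months, and let S of those A no longer use TRE once a week. Count non-attenders as not retained. Then:

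- drop-out = 1 − A/50
- retention as defined = (A − S)/50
- sum = 1 − S/50

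The two add to 100% only if S = 0. Each person counted in S removes 1/50 = 2 percentage points. The Subject withdrawal section provides for such people, so S = 0 cannot be presumed.

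**3. What the rate says about adherence.** Take an illustrative cohort of 50, with 20 people at 1 day a week, 15 at 3 and 15 at 6. Mean adherence is (20×1 + 15×3 + 15×6)/50 = 155/50 = 3.1 days a week. Retention as defined is 100%, while 15/50 = 30% reach five or more days.

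**4. The time window.** The definition does not say whether it refers to the week before the visit or to every week so far. Suppose, for illustration, that days are independent with daily probability p. The chance of at least one TRE day in a week is 1 − (1 − p)^7. The chance of meeting this in all 12 weeks is that value to the 12th power.

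| p | week before the visit | every one of 12 weeks |
|---|---|---|
| 1/7 | 0.660 | 0.007 |
| 2/7 | 0.905 | 0.30 |
| 3/7 | 0.980 | 0.79 |

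Independence is an assumption, and the results depend on it. At 2/7 (29% of days), if each week is followed either on all seven days or on none, the week-before rate is 2/7 = 29%. If everyone follows exactly two days every week, it is 100% under either reading.

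At n = 50 the 95% half-width of a proportion is at most 1.96 × √(0.5 × 0.5/50) = 0.139, about 14 points. At p = 2/7 under independence, the two readings differ by 0.905 − 0.30 ≈ 0.60, or 60 points.

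**5. The comparison.** The direction of any distortion is not fixed. Against an attendance rate, the TRE figure is the lower quantity by S/50 in step 2, which works against TRE. Against a stricter adherence measure, the lenient threshold works in favour of TRE. The Protocol does not say which applies.

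**The case against.** Much can be said for the plan. Mean adherent days is the primary outcome and retention is monitored alongside it. A cohort using TRE one day in seven would show about 12 of 84 days, so poor adherence would be visible. Attendance at 3 months is covered by the drop-out rate, which can be compared across cohorts. Separating people who stop TRE from people who stop attending is sensible, and the retention measure can be read as continued use under an unfortunate label. All of this stands and limits the harm.

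Four stronger readings are tempting, and the document supports none of them:

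- *Near-total non-adherence would count as success.* No success threshold is attached to retention.
- *The rate stays high whenever adherence is poor.* That needs the week-before reading and a particular pattern of days. Under independence with every week required, the figure at 2/7 is about 30%, not 90.5%.
- *The measure cannot be computed in earlier cohorts.* What those cohorts recorded is not shown, and their use of other methods is inferred from the Synopsis and Secondary Outcomes. The document shows only that no counterpart is defined.
- *The 6-month item collects the wrong unit.* A count of weeks can fit a once-a-week threshold, and measuring use after the three-month period is legitimate. The gap is that an adherent week is not defined there.

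The objection does not reach the label, the absence of attendance rates at 6 weeks and 6 months, or the undefined comparator.

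**Conclusion.** The point holds as one of definition and comparability. A named part of the primary objective is a minimal-use threshold (14% of prescribed days) called retention. It departs from the complement of drop-out by 2 points for each participant who attends but no longer uses TRE weekly. Its time window is open, and under independent days that choice alone can move the figure by more than sampling error does at n = 50. The planned cross-cohort comparison of this rate has no stated like-for-like basis, and the direction of the resulting error cannot be known from the Protocol.

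The 14% and the 2 points follow from the text, the latter with non-attenders counted as not retained. The probabilities are illustrative. The conclusion about the comparison assumes that the earlier cohorts used methods other than TRE, as the Protocol's wording implies. The feasibility assessment as a whole is not invalidated, since mean adherent days and 3-month drop-out remain usable.

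**What to change.** - Define retention at 6 weeks, 3 months and 6 months as attendance at that visit, over all enrolled. At 3 months it is then exactly the complement of drop-out. Do not widen it to data obtained by other means, because someone who missed the 3-month visit could then be both retained and a drop-out.
- Compare only attendance-based retention and drop-out with earlier cohorts.
- Report the present measure separately, without cross-cohort comparison, as continued TRE use (at least one day a week). State whether it refers to the week before the visit or to every week so far.
- Label the 6-month value as use after the three-month intervention period, and align the 6-month item by defining an adherent week as one with at least one TRE day.
- The Subject withdrawal section names only 6 weeks and 3 months for people who stop TRE. State whether they are also invited at 6 months, since an all-enrolled rate would otherwise count them as non-attenders.

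The cost is a wording change and a simple attendance tabulation from visits already scheduled.

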**Secondary Outcomes**

- Changes in weight from baseline to 6 weeks, and to 3 months and 6 months.
- Changes in blood pressure from baseline to 3 months and 6 months,
- Changes in lipid profile from baseline to 3 months;
- Participant feedback and ratings of the intervention, including the helpfulness of the intervention, recommending it to friends, readiness to continue, barriers and facilitators, and most popular 8-hour time frames.
- Changes in ratings of the difficulty adhering to TRE and ratings of hunger over time
- Estimates of effect size for future randomised trials, if TRE is deemed feasible and efficacy is encouraging.
- Comparison of weight changes in TRE to weight changes in other weight-loss cohorts in our previous trials and community clinics.

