**Study Design**

Cohort follow-up.

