# STATISTICAL CONSIDERATIONS

**Sample Size**

In this early phase exploratory research, we opted for a pragmatic sample size of 50, achievable economically and quickly, but large enough to provide reasonable confidence intervals on key estimates.

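### The pilot promises effect sizes for a future randomised trial, conditional on encouraging results, but a single cohort offers no contrast that estimates a randomised between-arm difference

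*Protocol*

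**What the plan says.** The Secondary Outcomes section of the protocol includes "Estimates of effect size for future randomised trials, if TRE is deemed feasible and efficacy is encouraging". The Secondary Objectives section carries the same condition: it requires that the intervention be "feasible and the efficacy results are encouraging, effect estimates to inform" any later randomised trial, and it describes the changes in weight, blood pressure and lipids as effects of TRE. Neither section says what counts as encouraging. The Synopsis makes it an aim to judge whether a larger controlled trial would be worthwhile, so this output serves a main purpose of the pilot.

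Study Design reads, in full, "Cohort follow-up". Statistical Analysis offers two contrasts:

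- Within the cohort: "Paired samples t-test will be used to examine any significant changes from baseline to follow-up in weight, BMI, blood pressure, and blood lipid profiles".
- Against external data: "Adherence rates to TRE and weight/BMI changes will be compared against previous weight-loss intervention cohorts". Secondary Outcomes lists the weight part of this without any condition: "Comparison of weight changes in TRE to weight changes in other weight-loss cohorts in our previous trials and community clinics".

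The protocol does not say which of the two would supply the effect size. The changes in weight, blood pressure and lipids are themselves unconditional secondary outcomes.

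**The concern.** A randomised trial is sized on the expected difference between its arms. The before-after change in one cohort also contains whatever would have happened without TRE. Participants here volunteer through advertisements or come from a weight clinic, have clinic visits at weeks 1 and 6, and are telephoned in weeks 2 to 5. Any change due to motivation or contact is counted with the intervention. The comparison with earlier cohorts does have a second group, but that group was not randomised and received other weight-loss interventions. Its bias can go either way, and its comparator need not be the one a future trial would use.

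The condition adds a second problem. If a figure is offered for planning only after the results look good, chance overestimates are more likely to pass the filter than chance underestimates. At stake is the target difference, and hence the size and power, of the trial that this pilot is meant to inform.

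**Working it through.** **The plan's own figure.** The only number is the sample size of 50. It is called pragmatic and justified as "large enough to provide reasonable confidence intervals on key estimates". No alpha, power, effect, SD or target interval width is given, so it cannot be reproduced. For orientation, with all 50 observed, the 95% half-width is 1.96 × √(0.25/50) = 0.139, or 13.9 percentage points, for a proportion of 50%. For a mean change it is t(0.975, 49)/√50 = 0.28 SD.

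**Selection on a favourable result.** Inputs: n = 50 from the protocol. Assumed: encouraging means a paired change in the favourable direction at two-sided p<0.05, and the estimate is normal. Let d be the true standardised change, se = 1/√50 = 0.141 and c = 1.96 × se = 0.277. The mean estimate among studies that pass is

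E = d + se × φ(a)/(1 − Φ(a)), with a = (c − d)/se.

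For d = 0.2: a = 0.546, φ(a) = 0.344, 1 − Φ(a) = 0.293, so E = 0.2 + 0.141 × 0.344/0.293 = 0.37.

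| True change (SD) | Chance of passing | Mean reported (SD) | Inflation |
|---|---|---|---|
| 0.2 | 29% | 0.37 | 1.83 |
| 0.3 | 56% | 0.40 | 1.33 |
| 0.5 | 94% | 0.52 | 1.03 |
| 0.8 | 100% | 0.80 | 1.00 |

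In kilograms, with an assumed SD of 4 kg and 40 participants with data, a true loss of 1.0 kg would be reported on average as 1.67 kg. A trial sized on that would have (1.0/1.67)² = 36% of the number needed. A true loss of 3 kg would be reported as about 3.01 kg, which is no material inflation.

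**Before-after change used as the between-arm difference.** All inputs are assumed: a 3 kg loss in the cohort, SD of change 4 kg in each arm, two-sided alpha 0.05, 80% power, 1:1 allocation. Number per arm = 2 × (1.96 + 0.84)² × 4²/Δ², rounded up. Sizing on Δ = 3 gives 28 per arm. The true Δ is 3 minus the control-arm loss.

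| Control-arm change | True Δ (kg) | Needed per arm | Needed ÷ 28 | Power with 28 per arm |
|---|---|---|---|---|
| gains 0.5 kg | 3.5 | 21 | 0.75 | 91% |
| none | 3.0 | 28 | 1.00 | 80% |
| loses 0.5 kg | 2.5 | 41 | 1.46 | 65% |
| loses 1 kg | 2.0 | 63 | 2.25 | 46% |
| loses 1.5 kg | 1.5 | 112 | 4.00 | 29% |
| loses 2 kg | 1.0 | 252 | 9.00 | 15% |

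The direction of the error depends on what controls would do, and a single cohort cannot show that.

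**The case against.** Much of the case on the other side stands.

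- *Nothing is suppressed.* The changes are unconditional outcomes with an unconditional analysis. The condition governs only whether they are put forward as planning inputs, and one may say that none are needed if no trial follows. This limits the harm, but the item labelled for planning is the one a later sample size would draw on.
- *The protocol never names the before-after change as the effect size.* True. But the only alternative it plans is the historical comparison, which is not a randomised contrast either, so leaving the source open does not solve the problem.
- *Removing the condition does not remove selection.* A trial will be planned only after a good pilot, whatever the wording. This is correct, and it is why the target difference has to come from elsewhere.
- *This is an exploratory pilot with a feasibility objective.* That is a reason to confine its outputs to what it can estimate.

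A reader might also infer that Sample Size, which relies on confidence intervals, contradicts Statistical Analysis, which plans to "examine any significant changes from baseline to follow-up" and mentions no intervals. The protocol does not exclude intervals, a paired t-test yields one directly, and such detail is commonly left to an analysis plan. The same applies to the missing threshold for going ahead. Neither is counted here.

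**Conclusion.** The point holds as a limit on what the design can deliver. The protocol promises an effect size for a randomised trial that neither of its contrasts estimates, and it makes that promise depend on a favourable result.

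A reader might go further and conclude that the effect size will be inflated and the next trial undersized. The protocol does not support that. The filter inflates materially only when the true change is small relative to its standard error, and hardly at all when it is large. The before-after change undersizes a trial only if controls also lose weight, and oversizes it if they gain. No future sample size or target difference is stated, so there is no wrong figure to correct. The SD, the number with data, the reading of encouraging as p<0.05 and the control-arm changes used above are all assumptions. The illustrations span no inflation to 1.83-fold with 50 participants, and a need of 0.75 to 9 times the naive number per arm.

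**What to change.** In Secondary Objectives and Secondary Outcomes:

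1. Delete the condition on feasibility and encouraging efficacy.
2. Replace the wording that presents the changes as effects of TRE, and as effect sizes for randomised trials, with within-group changes. Report each as n, mean, SD and 95% CI whatever the result.
3. State that the pilot supplies the SD of change, adherence, retention and drop-out for planning.
4. State that the target difference for any future trial will be justified separately, for example as a minimum important difference, and not taken from the uncontrolled change or the historical comparison.

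The first change without the fourth would leave the problem in place. No visits, participants or measurements are added. The cost is that the pilot no longer offers an effect size for the next trial.
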